**3. Methods**

3.1. Study Design:

A observational case-control study with individual matching for age and sex.

3.2. Setting:

Kikwit is the largest city of [Bandundu Province](http://en.wikipedia.org/wiki/Bandundu_(province)), lying on the [Kwilu River](http://en.wikipedia.org/wiki/Kwilu_River) in the southwestern part of the [DRC](http://en.wikipedia.org/wiki/Democratic_Republic_of_Congo). The population is approximately 350,000. The situation in DRC is dramatic in terms of health provision, with a weak health system, extremely poor accessibility of the existing health system and regular emergency levels of mortality figures, even in stable districts. These negative indicators are the result of, amongst others, decades of civil war and unrest, poor infrastructure and challenging geographical features, and poor management of the existing resources.

The sanitary district of Kikwit lies about 500 kilometers east of the capital, Kinshasa. It has a supervisee of 330 km² and a population density of approximately 1282 habitants per km². It is composed of 2 “zones de santé”:

- ZS de Kikwit Nord (161,046 habitants), 18 “aires de santé”, comprising 2 communes: Lukolela et Nzinda.
- ZS de Kikwit Sud (176,300 habitants), 15 “aires de santé”, comprising 2 communes: Lukeni et Kazamba

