## 3.4. Study population

The study population consisted of TF cases randomly selected from the line list of cases who are living within 7 out of the 33 “aires de santé”, believed to be hotspots of TF transmission within Kikwit.

The case definition during the outbreak was provided jointly by the Ministry of Health and the World Health Organization. A **Suspected case** is any person with gradual onset of steadily increasing and then persistently high fever, malaise, headache, sore throat, cough, and, sometimes, abdominal pain and constipation or diarrhea. A **Confirmed case** is asuspected case confirmed by isolation of *Salmonella* Typhi from blood, bone marrow, duodenal fluid or stool. For the confirmation of TF, isolation of *Salmonella* Typhi is required. Blood culture is the mainstay of the diagnosis. In endemic areas, stool isolation alone is insufficient for diagnosis if the clinical picture is not complete.

Two controls of the same sex, age class (10 to 14, 15 to 19, 20 to 29, 30 to 39, 40 to 49 and more than 50) and “aire de santé” will be selected per case. Selection criteria for controls are not having been suspected of TF during the study period and having the possibility to present themselves at the health structure during the study period if required.

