## 3.6. Sampling procedure

A representative sample of cases will be selected by random sampling, using random numbers generated in MS Excel, from a line list of cases who are living within the 7 “aires de santé” believed to be hotspots of TF transmission within Kikwit. Controls will be selected in two phases.

In the first phase, a geo-referenced polygon around each of the the 7 “aires de sante” will be generated from images obtained from Google Earth. Then with the help of the software package R, a total of 1500 random points will be generated within this polygon and the geographic coordinates of each point will be registered. Again, with the help of Google Earth images, all the points not falling on the roof of a house will be eliminated. Finally, 640 houses will be selected at random from the remaining points and allocated to cases: the first and the second point will be allocated to case 1, the third and fourth to case 2, and so on. As such, each case of the study population will have 2 random points allocated that each correspond to a house within the polygon.

In the second phase, with the help of a GPS, the corresponding houses will be visited by field teams. Within the household, a control will be recruited, matching the corresponding case in sex and age, and without suspicion of TF during the study period. If within this household no one matches the case or no one corresponds to the control criteria, then the field team will survey the next occupied building to the right. A household is defined as a group of people sleeping in the house and sharing the meals regularly during the study period.

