## 3.7. Study period

## This case control survey will be carried out in Kikwit between November 2012 and February 2013 and is related to the TF outbreak that struck Kikwit between November 14th and December 25th 2011.

## 3.8. Study procedures

A semi-structured questionnaire was developed to gather information on the presence or absence of TF morbidity in conjunction with various factors (basic socio-demographics; water source/s, storage capacity, and point-of-use treatment; hygiene and sanitation practices; food and drink consumption; and health seeking behavior). The number of questions was limited to be amenable. The survey questionnaire is provided as Annex I. Information was collected both at the level of individual respondent and of each household as a whole. On consultation with national staff, the minimum age for respondents was set at 10 years.

The questionnaire was translated from English to French, back-translated by a second translator for verification, and piloted in an area of Kikwit not included in the selected sample. The survey team will comprise of residents of Kikwit (both men and women), coordinated by supervisors. The supervisors will control the quality of completed forms and data entry, and additional random checks will be carried out by the survey coordinator.

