3.9. Sources of data

Sources of data are as follows: official data from the Ministry of Health registers (line list) will be used to describe the previous epidemics in terms of person, time and place. This line list has been created by the MOH in order to register every suspected case of TF, and contains several items of interest such as name, address, sex, age, date of onset, date of admission, symptoms at admission, status, results of laboratory analysis and outcome.

Population data (denominators) used for rate estimations will be obtained from the census bureau in Kikwit.

Complementary sources of information will be:

- interviews with the health authorities of the concerned area.
- environmental evaluations in the most affected area’s.
- visit to the reference hospital.
- visit to the reference laboratory.
- chemical and biological water tests.

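### Control eligibility turns on an undefined suspicion of typhoid over an unclear period, so people ill in the 2011 outbreak could be enrolled as controls

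*Protocol*

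**What the plan says.** Section 3.4 of the protocol sets two criteria for a control: "not having been suspected of TF during the study period and having the possibility to present themselves at the health structure during the study period", the latter if required. Section 3.6 tells the field team to recruit a household member "matching the corresponding case in sex and age, and without suspicion of TF during the study period", and to move to the next occupied building if nobody qualifies.

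Section 3.4 also defines a suspected case, by symptoms: it "is any person with gradual onset of steadily increasing and then persistently high fever, malaise, headache, sore throat, cough", sometimes with abdominal pain and bowel symptoms. Cases are sampled from the Ministry of Health register described in section 3.9: "This line list has been created by the MOH in order to register every suspected case of TF". That register holds name, address, admission date and symptoms at admission.

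Section 3.7, headed as the study period, says the survey "will be carried out in Kikwit between November 2012 and February 2013 and is related to the TF outbreak" of 14 November to 25 December 2011. Section 3.8 says the questionnaire is meant to "gather information on the presence or absence of TF morbidity in conjunction with various factors", health-seeking behaviour among them. Section 3.13 compares simple cases, complicated cases and respondents who had no typhoid in the 2011 outbreak.

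**The concern.** The analysis needs controls who did not have typhoid in the 2011 outbreak. The eligibility rule does not secure this, for two reasons.

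- **The criterion has no stated method.** Being suspected is something done to a person, and the protocol does not say by whom. It could mean recognition by a health service, presence on the line list, or a history that fits the symptom definition. Interviewers could apply different rules. On the first two readings, a person who was ill at home in late 2011 and treated themselves qualifies as a control.
- **The period is ambiguous.** The section that defines the study period gives the survey dates and the outbreak dates. If the survey dates apply, suspicion need only be absent from November 2012 to February 2013, and a person listed in 2011 might qualify.

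The ability-to-attend criterion closes neither gap. It asks whether a person could attend, not whether they were ill and did not.

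Controls come from the seven health areas believed to be transmission hotspots, where unrecorded illness is most likely to be found. If such people share the exposures of cases, they bring the control group closer to the cases. This cannot be reliably repaired after recruitment.

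**Working it through.** **Inputs.** From section 3.5: odds ratio 1.5, 80% power, exposure 30% in controls, two controls per case, 320 cases and 640 controls. From the Introduction: 1438 reported cases and about 60,000 people in the hotspot zones. Assumed: two-sided 5% level (not stated), unmatched formulas, and c, the share of controls who were in truth ill (not given).

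**1. The plan's own figure.** Case exposure is p1 = 1.5 × 0.30 / (0.70 + 1.5 × 0.30) = 0.3913. The pooled proportion is (0.3913 + 2 × 0.30)/3 = 0.3304.

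n = [1.960 × √(1.5 × 0.3304 × 0.6696) + 0.842 × √(0.3913 × 0.6087 + 0.30 × 0.70/2)]² / (0.0913)² = 316 cases.

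This is close to the stated 320. A matched-set formula with no exposure correlation also gives 316. Power at 320 and 640 is 80.5%, so there is almost no reserve.

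**2. Dilution.** Suppose a share c of controls were ill and have the same exposure as cases. Control exposure is then (1 − c) × 0.30 + c × 0.3913. The observed odds ratio is the odds of 0.3913, which is 0.6429, divided by the odds of that mixture. At c = 10%, for example, the mixture is 0.3091, its odds are 0.4475, and 0.6429/0.4475 = 1.44.

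| c (assumed) | Control exposure | Observed OR | Power at 320/640 | Cases needed for 80% |
|---|---|---|---|---|
| 0 | 0.3000 | 1.50 | 80.5% | 316 |
| 2.4% | 0.3022 | 1.48 | 78.6% | 332 |
| 5% | 0.3046 | 1.47 | 76.3% | 352 |
| 10% | 0.3091 | 1.44 | 71.6% | 393 |
| 20% | 0.3183 | 1.38 | 61.2% | 501 |

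**3. What the shares would mean.**

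- If all 1438 reported cases lived in the hotspot zones, 1438/60,000 = 2.4% of residents were listed. This is an upper bound, for all ages together. It is roughly the contamination to expect if listed cases could be drawn as controls.
- Unlisted illness equal in number to listed illness gives nearly the same share: 1438/(60,000 − 1438) = 2.5%.
- A share of 10% needs 0.10 × 58,562 = 5856 unlisted ill people, which is 5856/1438 = 4.1 for each listed case. If fewer of the listed cases lived in the hotspots, the multiple is higher.

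**The case against.** Several stronger readings are tempting, and the documents do not support them.

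- **That absence of suspicion is the only requirement.** It is not. Section 3.4 adds the ability to attend, which limits non-attendance through lack of access, though not through choice.
- **That the label requires contact with a health worker.** This is an inference. The suspected-case definition in section 3.4 is purely symptomatic. Applied to controls, it would exclude a person who was ill at home. The register described in section 3.9 makes the health-service reading natural, but the text does not settle it.
- **That controls are asked nothing about symptoms.** This cannot be said. Section 3.8 covers typhoid morbidity, and the questionnaire in Annex I is not in the text at hand. What can be said is that the visible text does not make any answer a condition of eligibility.
- **That missed illness must have been common.** The protocol does speak of "extremely poor accessibility of the existing health system", but that sentence describes the country as a whole. For Kikwit, section 3.3 describes free treatment, trained health-centre staff, an implemented case definition and community awareness work. These may reduce missed cases, but they cannot be assumed to remove them.
- **That every odds ratio moves towards 1.** This holds only where missed cases have case-like exposures. People who did not seek care may differ in exposures such as the cost or source of water, and the direction is then not fixed.

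What remains of the case against is that the effect is small unless unlisted illness was several times the listed number. What remains of the concern is that neither the criterion nor its period is defined.

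**Conclusion.** The point holds as a gap in the eligibility rule. Sections 3.4 and 3.6 do not say whose suspicion counts or how its absence is established, and section 3.7 does not fix the period. Under plausible readings, unreported or even listed 2011 cases can enter as controls. The documents do not show that this would happen, or how often.

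The loss is modest at 2.4% contamination and more material at 10%, where it takes about nine percentage points (80.5% − 71.6% = 8.9) from a design with almost no spare power. These figures rest on an assumed share, case-like exposure in the people misclassified, a two-sided 5% level and unmatched formulas. The change is worth making because it costs little and must be made before recruitment.

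**What to change.** In sections 3.4 and 3.6, define a control as a person who, for 14 November to 25 December 2011:

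(a) is not on the Ministry of Health line list, checked by name and address; and
(b) reports no illness that fits the section 3.4 suspected-case picture as a whole, not any single symptom, asked with a fixed list at screening.

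If either fails, the team goes to the next house as section 3.6 already provides. Record the number excluded and the reason. Name the outbreak dates in the criterion rather than referring to the study period.

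The two limbs do different work: (a) catches only listed cases, and (b) addresses the unlisted ones.

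The cost is a few screening questions, a look-up in a list already used to sample cases, and some extra houses. Limb (b) relies on recall over about 10 months (25 December 2011 to early November 2012) to 15 months (14 November 2011 to February 2013). It will also exclude some people who had another febrile illness, and the count of exclusions makes that visible.

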## 3.7. Study period

## This case control survey will be carried out in Kikwit between November 2012 and February 2013 and is related to the TF outbreak that struck Kikwit between November 14th and December 25th 2011.

## 3.8. Study procedures

A semi-structured questionnaire was developed to gather information on the presence or absence of TF morbidity in conjunction with various factors (basic socio-demographics; water source/s, storage capacity, and point-of-use treatment; hygiene and sanitation practices; food and drink consumption; and health seeking behavior). The number of questions was limited to be amenable. The survey questionnaire is provided as Annex I. Information was collected both at the level of individual respondent and of each household as a whole. On consultation with national staff, the minimum age for respondents was set at 10 years.

The questionnaire was translated from English to French, back-translated by a second translator for verification, and piloted in an area of Kikwit not included in the selected sample. The survey team will comprise of residents of Kikwit (both men and women), coordinated by supervisors. The supervisors will control the quality of completed forms and data entry, and additional random checks will be carried out by the survey coordinator.

## Households will be selected as described above and interviews will be conducted. Interviewers will request to be shown any household water storage receptacles and latrines present at the end of each interview. The locations of principal water sources for each household will be identified using information collected in the questionnaire, and their positions will be recorded using hand-held Global Positioning System (GPS) devices. Locations will be cross-referenced, where possible, against information available from other actors for verification purposes.

3.9. Sources of data

Sources of data are as follows: official data from the Ministry of Health registers (line list) will be used to describe the previous epidemics in terms of person, time and place. This line list has been created by the MOH in order to register every suspected case of TF, and contains several items of interest such as name, address, sex, age, date of onset, date of admission, symptoms at admission, status, results of laboratory analysis and outcome.

Population data (denominators) used for rate estimations will be obtained from the census bureau in Kikwit.

Complementary sources of information will be:

- interviews with the health authorities of the concerned area.
- environmental evaluations in the most affected area’s.
- visit to the reference hospital.
- visit to the reference laboratory.
- chemical and biological water tests.

## 3.10. Chemical and biological water tests

## No major improvements have been made to the water distribution infrastructure since November 2011, and water quality testing can thus still be performed, as results are likely to reflect the conditions of 2011. Two tests will be used to evaluate the quality of water being consumed: a test to measure the free residual chlorine and a test to evaluate the presence of coliform bacteria. The chlorine test will be performed on water samples collected from the household water reservoir and when possible from the water source used by the household. This will be done using a spectrometer HANNA HI 701 Checker © HC² (HANNA ©Instruments, USA). The level of 0,2 mg/l will be considered as sufficient to consider the water as potable. The test of presence of coliforms will be done only on a water sample collected from the household water reservoir with the help of the test AquaCHROM TM (CHROMagar TM, France).

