In Kikwit, the environment is mountainous with in the extreme north the river Kwilu. Between the different mountains exist small rivers and springs. Availability of potable water is challenging, especially in “Kikwit ville basse”, the lower lying part of Kikwit town. Piped water is too expensive for most of the population and its quality is compromised by inappropriate chlorination, and a leaking distribution network that allows aspiration of surface water when the pumps stop turning and the water pressure drops within the network. The price of the water also compromises its accessibility considerably. As a coping mechanism, the population uses open, unprotected springs to collect drinking water. Up to four or five springs can be identified per “aire de sante” and they well up at the bottom of the slopes in this mountainous environment. These sources are often situated close to small tributary rivers of the main river Kwilu. Only about 50 % of people in Kikwit own a latrine and wild defecation is rampant, also uphill of springs, leading to a high-risk environment for TF transmission. The central market of Kikwit also has an important potential to maintain TF transmission, with an absence of water and hand washing points on the market itself. Only one individual is responsible for cleanness in the market and most goods are presented on the ground instead of on tables. No latrines are available on the market.

3.3. Study site:

MSF is supporting Kikwit Nord General Hospital in order to offer free and quality treatment to simple TF patients as well as to those suffering from complications or perforation. Simple cases are given outpatient care and antibiotics, while complicated cases are hospitalized and perforated cases receive surgical treatment. MSF also provides medicines to the hospital, gives training to the personnel of the hospital and health centers around the city, and ensures that an adequate case definition and treatment protocol are implemented. Community workers are raising awareness among the population about basic hygiene practices, in order to halt this serious epidemic of TF, the so-called "dirty-hands disease”. These interventions are part of an emergency response, despite the fact that the problem is systemic and has repeated itself each 5 years in Kikwit.

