## 3.12. Variables

For each respondent, all variables contained in the survey questionnaire will be collected. The study is centered on demographics and household composition, household water sourcing and storage, hygiene practices, and food/drink hygiene practices. The variables collected are listed in full in the questionnaire in Annex I. Additionally, variables pertaining to water quality will be collected per household (cf. §3.10.).

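### Unchanged distribution infrastructure does not justify reading household-reservoir chlorine and coliform results from 2012-13 as 2011 exposures

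*Protocol*

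**What the plan says.** Section 3.7 states that the survey "will be carried out in Kikwit between November 2012 and February 2013". The illness under study is about a year older, since by the same section the survey "is related to the TF outbreak that struck Kikwit between November 14th and December 25th 2011". Section 3.10 nevertheless takes water tests made during the survey to describe the outbreak period. Its only stated reason is "No major improvements have been made to the water distribution infrastructure since November 2011", from which it concludes that "water quality testing can thus still be performed, as results are likely to reflect the conditions of 2011".

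The same section fixes the sampling points. Chlorine is measured on "water samples collected from the household water reservoir and when possible from the water source used by the household". For the microbiological test: "The test of presence of coliforms will be done only on a water sample collected from the household water reservoir".

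Section 3.12 adds that "variables pertaining to water quality will be collected per household". Section 3.13 plans bivariate and multivariate analysis and groups respondents by their typhoid status in the 2011 outbreak. Section 3.3 records, as part of the emergency response, that "Community workers are raising awareness among the population about basic hygiene practices".

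**The concern.** The reason given concerns the supply network, but most of the measurements are made in the home. What is in a household reservoir depends on which source the household now uses and on how it stores and treats the water. Section 3.8 itself lists source, storage and point-of-use treatment among the factors the questionnaire covers, so the protocol recognises household practice as something separate from supply. Section 3.2 adds that piped water is beyond the means of most residents, who draw from open springs. For them the state of the pipes says little even about the source.

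The reservoir sample is therefore an exposure measured after the disease and open to change by it. A household that had a typhoid case may since have begun to treat or cover its water. If that happened more often in case households than in control households, unsafe stored water in 2011 would appear less harmful than it was. The aim in section 2 is to recommend interventions, and section 4.3 hopes that the results will help obtain funds for water infrastructure. A null reservoir result misread as a 2011 exposure would bear on both.

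**Working it through.** **Timing.** From the end of the outbreak (25 December 2011) to the first possible visit (November 2012) is about 10 months. From its start (14 November 2011) to the last (end of February 2013) is about 15.5 months.

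**What the stated reason covers.**

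- Source chlorine: partly covered, for households on the network. It is taken only where possible.
- Reservoir chlorine: not covered.
- Reservoir coliforms: not covered, and there is no source-level coliform test to fall back on.

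**The plan's own figure.** Section 3.5 gives an odds ratio of 1.5, exposure in controls p0 = 0.30, 80% power, two controls per case, and 320 cases with 640 controls. Alpha is not stated; two-sided 0.05 is assumed, and matching is ignored.

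- Exposure in cases: p1 = 1.5 × 0.30 / (0.70 + 1.5 × 0.30) = 0.45 / 1.15 = 0.391.
- The usual two-proportion formula with pooled variance and a 2:1 ratio gives 316 cases, and power at 320/640 is 80.5%. The stated size is reproduced. The sample size is not at fault here.

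**Illustration of the bias.** Let r1 and r0 be the shares of case and control households with unsafe stored water in 2011 that have become safe by the visit. These shares are assumptions; the protocol gives none. Then:

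- observed prevalence in cases a = p1(1 − r1), in controls b = p0(1 − r0);
- observed odds ratio = [a/(1 − a)] / [b/(1 − b)].

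| r1 (cases) | r0 (controls) | a | b | Observed OR |
|---|---|---|---|---|
| 0% | 0% | 0.391 | 0.300 | 1.50 |
| 10% | 0% | 0.352 | 0.300 | 1.27 |
| 20% | 0% | 0.313 | 0.300 | 1.06 |
| 20% | 10% | 0.313 | 0.270 | 1.23 |
| 20% | 20% | 0.313 | 0.240 | 1.44 |
| 30% | 0% | 0.274 | 0.300 | 0.88 |
| 30% | 10% | 0.274 | 0.270 | 1.02 |
| 40% | 10% | 0.235 | 0.270 | 0.83 |
| 0% | 10% | 0.391 | 0.270 | 1.74 |

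For the row 20%/0%: a = 0.391 × 0.80 = 0.313, odds 0.313/0.687 = 0.456; control odds 0.30/0.70 = 0.429; ratio 1.06.

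**Where the association vanishes.** Setting a = b gives r1 = 1 − p0(1 − r0)/p1. With no change in controls this is 1 − 0.30/0.391 = 23%. With 10% change in controls it is 1 − 0.27/0.391 = 31%. Reversal needs more than that.

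**Power.** With no change in controls, 10% change in cases lowers power at 320/640 from about 80% to about 37%.

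The rows separate two effects. Equal change in both groups costs little (1.44). It is the difference between the groups that matters, and its sign decides the direction: more change in controls would inflate the odds ratio, as the last row shows.

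**The case against.** Three points on the other side have weight.

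- **Use in the model is inferred.** Section 3.9 lists the water tests among complementary sources, section 3.12 says only that the variables are collected, and section 3.13 does not name the variables in the multivariate model. A statistical analysis plan might restrict them to description. This stands as a limit. Still, the claim that the results reflect 2011 is in the protocol's own text, it invites an exposure reading, and nothing in the protocol restricts that reading.
- **Differential change has no source in the documents.** The promotion in section 3.3 was aimed at the population as a whole, so it reached controls too. It concerned basic hygiene, with no mention of water treatment or chlorine distribution. Section 3.2 describes constraints of price and supply that would limit change in any household. This also stands: more change in case households after illness and contact with care is plausible, not documented.
- **The questionnaire (Annex I) is not at hand** and may ask about changes since 2011. That would help interpretation, but it would not make a sample taken in 2012-13 a measurement of 2011 water.

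A reader might infer something stronger: that the reservoir results will hide or reverse a true risk factor. The documents do not support that. A clear reversal such as an odds ratio of 0.71 appears with 20% change in cases only if exposure in controls is put at 70%, a figure not in the protocol, and no control household changed. At the protocol's own 30%, that amount of change attenuates the association and does not reverse it.

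**Conclusion.** The point holds as a fault in the stated rationale. Unchanged distribution infrastructure may support reading source water as similar to 2011 for households on the network. It does not support that reading for reservoir chlorine or for coliforms.

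The consequence is conditional. If case households changed practice more than control households, a true association is attenuated. With a true odds ratio of 1.5 and 30% exposure in controls, 20% change in cases gives between 1.06 (no change in controls) and 1.44 (equal change). Reversal needs more than 23% change in exposed case households with none in controls, or more than 31% with 10% in controls. All these shares are assumptions.

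Confidence is high that the inference fails for reservoir samples, and moderate on the size and direction of any bias. Exposures that the questionnaire ties to 2011 are not affected by this point.

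**What to change.** In sections 3.10 and 3.13:

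- limit the statement about 2011 conditions to source water;
- describe reservoir chlorine and coliform results as water quality at the time of the visit;
- report them descriptively, or in a clearly labelled secondary analysis by 2011 typhoid status, and not as 2011 exposures in the main risk-factor model;
- take the water source and treatment reported for November-December 2011 as the main water exposure, and confirm that the questionnaire asks about that period;
- use source chlorine as supporting information only where the sampled source is the one the household used in 2011.

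The cost is mainly wording, and the planned tests stay the same. Two variables leave the main model, including the only microbiological one. The reported 2011 source and treatment are open to recall error over about a year, possibly different in cases and controls, and this should be stated as a limitation. Source chlorine will be missing where the source was not sampled or has changed, and may discriminate little among households that use open springs.
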